**Methods:**

The multimodal prehabilitation programme consists of an exercise programme, nutritional support, psychological support, smoking cessation, patient empowerment and respiratory optimisation. In two Dutch teaching hospitals, 40 adult patients with proven or suspected NSCLC will be included. In a non-randomised fashion, 20 patients follow the multimodal prehabilitation programme, and 20 will be assessed in the control group, according to patient preference. Assessments will take place at four time points: baseline, the week before surgery, 6 weeks postoperatively and 3 months postoperatively. Feasibility and indicative evidence of efficacy of the prehabilitation programme will be assessed as primary outcomes.

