### Participants

All consecutive patients meeting the inclusion criteria will be asked to participate in the multimodal prehabilitation programme. Patients are deemed eligible when ≥ 18 years of age, with pathologically confirmed or suspected NSCLC and an indication for anatomical lung resection. Furthermore, a straightforward preoperative work-up is needed to ensure patients can enter the programme directly after diagnosis in order to use the window of opportunity between diagnosis and surgery as efficient as possible. Also, the ability to provide written informed consent is needed for inclusion. Eligible patients not willing to participate in the multimodal prehabilitation programme will be asked to participate in the control group. The control group may provide insight in the course of functional capacity perioperatively and will enable comparison with the prehabilitation group.

Exclusion criteria comprise a contra-indication for training, renal insufficiency (defined as estimated glomerular filtration rate (eGFR) < 60 ml/min/1.73 m^2^) or participation in other trials that may interfere. Referred patients from another hospital with the diagnostic phase already completed will be excluded, for logistical reasons, travel distance and the probability that these factors may affect feasibility of the programme. If a contra-indication for training will become apparent after signing informed consent and following baseline assessment, we intend to exclude the subject from participation for safety reasons. Furthermore, if the postoperative pathology results will not confirm the diagnosis NSCLC, the data of this patient will be included in the analysis; however, we intend to recruit an extra patient to finally include a total of 40 patients with confirmed NSCLC, per centre ten patients in the prehabilitation group and ten in the control group. All assessed patients will be logged.

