The sample size of 40 participants for this feasibility study is based on a previously performed pilot study in colorectal cancer patients (Rooijen et al. 2019). This study was able to assess feasibility and indicative evidence of efficacy with a similar sample size. Patients will be selected and informed about the study during a visit to their treating pulmonologist in the outpatient clinic. Informed consent will be obtained by a member of the research team during a face-to-face consult in the outpatient clinic prior to baseline assessment. We intend to conduct the study and finish follow-up between January 2020 and January 2022. The SPIRIT-derived Fig. 1 displays an overview of the time points, assessments and recorded variables.

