#### Secondary outcomes

The following secondary outcomes will be studied:Programme evaluation as a whole and per intervention (based on compliance, patient satisfaction and experience of the research team)Effect on clinical outcome: 30-day mortality, length of hospital stay, 30-day complication rate expressed as the comprehensive complication index (Slankamenac et al. 2013) and readmission rate. This will be compared to the control group and a historical Dutch cohort as recorded in the DLCAs (Dutch Institute and for Clinical Auditing n.d.).Cost-effectiveness of the prehabilitation programmeEfficacy of the programme on nutritional and mental health status, smoking cessation and quality of life compared to baseline and control groupCorrelation between VO2max estimated with the physical condition questionnaire (FitMax^©^) and as determined with the SRT and, if applicable, CPET

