### Statistical analysis

Because of the sample size of the group, descriptive data will be presented as median (interquartile range and/or range). Categorical data will be presented as numbers and percentages. Results of validated questionnaires will be calculated, and missing data will be handled using the instructions from the original authors. Missing data which will be used in the definition of feasibility will be considered as “not performed”.

Feasibility will be descriptively evaluated (group level and patient level), both dichotomously (yes/no) and as percentage of the total number of offered interventions.

Comparative outcomes, such as functional capacity, between the different test moments will be compared within the group participating in the multimodal prehabilitation programme and within the control group with the Friedman test and between groups with the Mann–Whitney *U*-test. Nonparametric tests will be used because of the small sample size. Dichotomous data will be compared between groups with chi-square test. Mixed model analyses will be used to evaluate functional capacity over time.

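### One chi-square test is fixed for all binary comparisons at about 20 per group, with no rule for sparse or empty tables, so a single result can depend on which version is run

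*Protocol article*

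**What the plan says.** The Statistical analysis section of the protocol article sets the rule for binary outcomes in one sentence: "Dichotomous data will be compared between groups with chi-square test". It does not mention expected counts, a continuity correction or an exact alternative. Shortly before, in the same paragraph, it explains the choice for the other outcomes: "Nonparametric tests will be used because of the small sample size".

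The group sizes are in the abstract ("20 patients follow the multimodal prehabilitation programme, and 20 will be assessed in the control group") and in Participants ("per centre ten patients in the prehabilitation group and ten in the control group", at two centres). The total rests on precedent, not on a power calculation: "The sample size of 40 participants for this feasibility study is based on a previously performed pilot study in colorectal cancer patients".

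The binary outcomes concerned are under Secondary outcomes. The clinical list there includes 30-day mortality and readmission, and the article says of that list: "This will be compared to the control group and a historical Dutch cohort as recorded in the DLCAs". Smoking cessation is also to be compared with the control group. Two items on the clinical list are not binary: length of stay is a duration, and the complication outcome is an index score. The chi-square rule does not reach them.

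**The concern.** The authors recognised the small-sample problem and acted on it for continuous and ordinal outcomes. For binary outcomes they then named a large-sample approximation without qualification, although sparse tables are most likely there.

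Three things follow. First, the name 'chi-square test' covers both an uncorrected and a continuity-corrected version, and at this size the two can fall on opposite sides of 0.05 for the same table. Second, the test has no value when no patient in either group has the event, which is a realistic result for 30-day mortality. Third, smoking cessation can be assessed only in smokers, so that comparison has fewer than 20 per group unless every patient smokes, and the approximation is worse there.

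At stake is how single secondary results are labelled, and whether the choice of version is made before or after the data are seen.

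**Working it through.** **Inputs.** Taken from the article: 20 v 20, and chi-square for binary data. Assumed, because the article gives neither: a two-sided 0.05 level, and event rates of 1% to 30%. The 8 v 8 smokers' subset is also an assumption. Replacing patients whose NSCLC is not confirmed can raise the analysed number slightly above 20 per group; this is ignored here.

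**Stated sample size.** 2 centres × (10 + 10) = 40 = 20 + 20, which agrees. There is no power or alpha figure to reproduce.

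**Expected counts.** With equal groups the smallest expected count is min(events, 40 − events)/2. For the rarer category it is below 5 when 9 or fewer of 40 patients have the event (9/2 = 4.5; 10/2 = 5). The probability of this, from Binomial(40, rate), is:

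| Common event rate | P(9 or fewer events) |
|---|---|
| 1% to 5% | about 1.00 |
| 10% | 0.995 |
| 15% | 0.93 |
| 20% | 0.73 |
| 25% | 0.44 |
| 30% | 0.20 |

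**No events.** Pearson's X² = N(ad − bc)²/(product of the four margins). With no events in either group one margin is 0, so X² = 0/0. The chance of this is 0.99^40 = 0.67 at a 1% rate and 0.98^40 = 0.45 at 2%.

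**Two example tables.**

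4/20 v 0/20:
- Pearson: 40·(4·20 − 16·0)²/(20·20·4·36) = 256,000/57,600 = 4.44, p = 0.035.
- Yates: 40·(80 − 20)²/57,600 = 2.50, p = 0.114.
- Fisher: 2·C(20,4)/C(40,4) = 2·4,845/91,390 = 0.106.
- Boschloo: 0.061.

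6/20 v 1/20:
- Pearson: 40·(6·19 − 14·1)²/(20·20·7·33) = 400,000/92,400 = 4.33, p = 0.0375.
- Yates: 40·(100 − 20)²/92,400 = 2.77, p = 0.096.
- Fisher: 2·[C(20,6)·20 + C(20,7)]/C(40,7) = 2·852,720/18,643,560 = 0.092.
- Boschloo: 0.046.

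Boschloo's p-value is the largest probability, over all common event rates, of a table whose Fisher p-value is no greater than the one observed. The two groups of 20 are the fixed margins. The values were confirmed by direct enumeration.

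**All tables.** Over all 21 × 21 tables, every disagreement between Pearson and Fisher at 0.05 runs the same way: Pearson below, Fisher not. With Yates' correction no table is below 0.05 while Fisher is not.

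**Type I error at 20 v 20** (product of two Binomial(20, rate) distributions):

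| Common event rate | Pearson | Fisher |
|---|---|---|
| 2% | 0.0008 | 0.0001 |
| 5% | 0.012 | 0.002 |
| 10% | 0.039 | 0.012 |
| 20% | 0.050 | 0.023 |
| 25% | 0.051 | 0.024 |

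Pearson's maximum over all rates is 0.053. At 8 v 8 its maximum is 0.077, reached at a common rate of 50%.

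**The case against.** The strongest reply is that an expected count below 5 is only a rule of thumb, and that full enumeration is the proper check. Pearson passes it at 20 v 20: its error peaks at 5.3% and is far below 5% for rare events. Much of its gap from Fisher is Fisher's own conservatism. Barnard's unconditional exact test gives 0.039 and 0.049 for the two example tables, so it sides with Pearson. All of this stands. A reader might infer that the named test is invalid here and will produce spurious findings; the numbers do not support that for the full groups.

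A reader might also expect mortality to be falsely declared significant. That too is unsupported. A Pearson–Fisher disagreement needs at least 4 events against 0. With equal event rates in both groups, its probability is 0.007% at a 1% rate, 0.08% at 2%, 1.0% at 5% and 2.7% at 10%. For mortality the practical problem is the empty table.

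It can be said, too, that a continuity correction or a sparse-table fallback belongs in the full plan, which is not shown. That holds for the absence of planned intervals, which is not a finding on its own. Nor does the article suggest that a non-significant result will be presented as proof of no difference; it promises counts and percentages. But the test itself is named here without condition, so the point rests on what the article states.

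**Conclusion.** The point holds as a minor one. The article fixes an unconditional chi-square test for groups of about 20, against the small-sample reasoning in its own paragraph. Three consequences are established:

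- Sparse tables are the usual case for event rates clearly below 25%.
- The uncorrected test gives no result when no events occur, which is likely for 30-day mortality at an assumed 1% to 2%.
- The label attached to a single table can depend on an unstated choice of version, with p from 0.035 to 0.114 for 4 v 0 and from 0.0375 to 0.096 for 6 v 1.

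Average type I error is not materially inflated at 20 v 20. It can be in small subsets, but the 7.7% figure rests on an assumed 8 v 8, because the number of smokers is not given. Event rates and the 0.05 level are also assumptions. The outcomes are secondary, the study is a non-randomised feasibility study, and the selection and confounding bias that the article acknowledges matters more than the choice of test.

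**What to change.** Replace the chi-square sentence with:

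> Dichotomous outcomes will be compared between groups with an exact test (Boschloo's unconditional test, or Fisher's when any expected count is below 5) and reported as counts with a risk difference and 95% score-based confidence interval; 30-day mortality will be described with an exact interval and not tested.

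The switch to Fisher must be a fixed rule, because the two exact tests can differ: 6/20 v 1/20, with a smallest expected count of 3.5, gives 0.092 by Fisher and 0.046 by Boschloo. Using Boschloo's test throughout would avoid the switch. Either way, the two treatment groups should be entered as the fixed margins.

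The interval for mortality tells the reader more than a test would: 0/20 deaths has an upper exact 95% limit of 1 − 0.025^(1/20) = 0.168, about 17%.

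The cost is one sentence and no extra patients or data. The downside is slight conservatism, mainly with Fisher's test.

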## Discussion

Since many disciplines are involved and time is limited, multimodal prehabilitation is a logistic challenge. It is widely studied in patients with colorectal cancer and deemed feasible and effective (Rooijen et al. 2019; Trepanier et al. 2019; Scheede-Bergdahl et al. 2019). However, in the Netherlands, the recommended treatment interval for NSCLC is shorter compared to colorectal cancer due to tumour biology and mutual agreements amongst scientific societies and the DICA.

However, especially, the NSCLC population may particularly benefit from prehabilitation. The pulmonary system is one of the determinants of cardiorespiratory fitness, a measure interpreted as the reflection of total body health (Ross et al. 2016), as well as the organ system affected by NSCLC. Furthermore, the lung is the organ that is resected during surgery, thereby further compromising cardiorespiratory fitness in itself. Although improving cardiorespiratory fitness preoperatively will not prevent a decrease of functional capacity postoperatively, prehabilitation may limit the extent.

This protocol is a result of an extensive multidisciplinary project. Two clinical groups with expertise in perioperative recovery optimisation developed a protocol based on experience and available evidence, combining various interventions within a short timeframe. In order to make a patient-friendly programme, all disciplines need to optimise and harmonise planning.

To our knowledge, only one randomised controlled trial with a multimodal prehabilitation programme in a NSCLC population has been published; however, this concerned a non-supervised home-based programme with less interventions compared to our study (Liu et al. 2020). In the Netherlands, we experience a growing interest in prehabilitation prior to surgery, yet to date, there are no formal public prehabilitation programmes available for NSCLC surgery patients.

The results of prehabilitation are promising thus far in other cancer types (Minnella et al. 2021; Ploussard et al. 2020; Swaminathan et al. 2020). Since one of the primary aims of our study is to determine the feasibility — the main perceived barrier for application — of our multimodal prehabilitation programme, a study design based on randomisation was deemed suboptimal. Although a similar pilot study in patients with colorectal cancer did not find a better baseline functional capacity in the prehabilitation group compared to the control group (Rooijen et al. 2019), a selection and confounding bias may occur in our study. The control group in our study will put the prehabilitation group in perspective, since this enables us to determine the “normal” course in the perioperative period using data from the assessments and accelerometers. Additionally, studying the control group may help assess feasibility further.

In conclusion, with this study, we aim to examine if an extensive, mainly in-hospital multimodal prehabilitation programme is feasible in the limited preoperative period of maximum 3 weeks, as determined by our national guideline. Furthermore, we aim to study whether patient optimisation can be achieved. By publishing this protocol, we provide a detailed description of the programme to improve transparency. Hopefully, this may help other hospitals to shorten the process of multidisciplinary set-up and implement a multimodal prehabilitation programme more easily.

## Data Availability

Not applicable.

## Abbreviations

(Indirect) 1-RM: (Indirect) one-repetition maximum
6MWT: 6-Min walk test
ASz: Albert Schweitzer hospital
BIA: Bioelectrical impedance analysis
BMI: Body mass index
BSc: Bachelor of Science
Castor EDC: Castor electronic data capture
CCMO: Central Committee on Research Involving Human Subjects
COVID-19: Coronavirus disease 2019
CPET: Cardiopulmonary exercise test
DICA: Dutch Institute for Clinical Auditing
DLCAs: Dutch Lung Cancer Audit — Surgery
eCRF: Electronic case report form
eGFR: Estimated glomerular filtration rate
EORTC QLQ-C30: European Organisation for Research and Treatment of Cancer, quality of life of Cancer patient’s module
EORTC QLQ-LC13: European Organization for Research and Treatment of Cancer, quality of life of cancer patients lung cancer module
EQ-5D-5L: EuroQol group, 5-level general health-related quality-of-life questionnaire
ERAS: Enhanced recovery after surgery
ESTS: European Society of Thoracic Surgeons
FFM: Fat-free mass
GDPR: General Data Protection Regulation
HADS: Hospital Anxiety and Depression Scale
HIIT: High-intensity interval training
iMCQ: IMTA Medical Consumption Questionnaire
IMT: Inspiratory muscle training
iMTA: Institute for Medical Technology Assessment
iPCQ: IMTA Productivity Cost Questionnaire
ISI: Insomnia Severity Index
ISO: International Organization for Standardization
MD: Medical doctor
MIP: Maximal inspiratory pressure
MMC: Máxima MC
MSc: Master of Science
MSEC: Maximum short exercise capacity
NSCLC: Non-small cell lung cancer
PG-SGA: Patient-Generated Subjective Global Assessment
PhD: Doctor of philosophy
SPIRIT: Standard Protocol Items: Recommendations for Interventional Trials
SRT: Steep ramp test
VO2max: Maximal oxygen uptake
